#### Employment and income

Employment is measured using self-reports of the number of jobs held in the last year. Employment occurs (1) or not (0). Income is self-reported income above 1200 ZAR/month (1) or not (0).

#### Concurrent sexual partnerships and condom usage

Concurrent sexual partnerships are self-reported as having sexual partnerships overlapping in occurrence in the last 3 months (0) or not (1). Condom usage is always using condoms in the past 3 months (1) or not (0). No sex counts as (1).

#### Violence toward women

Violence against women is self-reported as threatening or perpetrating abusive behavior (physical and sexual; 0) or not (1).

#### Arrested

Self-reported arrest in the past 3 months as yes (0) or no (1).

#### Community activity

Self-reported as engaged in a community activity (1) or not (0).

#### Mental health

Mental health is evaluated by 20 items, each with a response range from 0 to 3, reflecting endorsement of symptoms of depression on the CES-D scale [47]. The scale has been found reliable (alpha > 0.85) in previous research [48]. Participants with a CES-D score greater than 16 are considered to have a depressed mood (0) and those < 16 are not (1).

### Secondary outcomes

#### HIV prevention and treatment continua

Among seronegative participants, self-reports document the utilization of repeat HIV testing, access of medical care, discussions of HIV prevention with sexual partners, and disclosure of serostatus. Among participants living with HIV, participants self-report engagement in medical care, uptake and adherence to antiretroviral (ARV) medications, and medical regimens over time. HIV testing is offered at the soccer fields by a mobile testing van and uptake is documented. Given the low self-reported rate of HIV positivity, we ask if participants want to share results as they test in real time at the 6-, 12-, and 24-month assessment. The key comorbidities affecting the HIV continua are included in the fifteen study outcomes (e.g., mental health symptoms, substance abuse, violence toward women).

#### Intermediate, mediating, and moderating factors

Consistency of daily routines: Sustaining a job requires consistent daily routines of waking up, going to work at the same time, being ready for work, preparing food, sleeping, etc. Interviewers ask young men to report their daily routines in the last 3 days: the number of meals eaten with others, time of going to bed and waking up, and whether household chores are done.

Density and centrality of social support networks: Similarly, interviewers ask the young men to list their friends and identify how often support (instrumental, emotional) is given or received, and the consequences of support received [52].

Quality of relationships with partner and father: These relationships are monitored from young men’s reports and include questions on their household members, allocation of household tasks, income contributions, discussion of health status, and mealtime involvement.

Community norms around HIV stigma, alcohol use, healthy nutrition, and hopefulness: Given HIV stigma is a major barrier to timely HIV testing and linkage to care, interviewers ask whether HIV is considered a punishment and whether it should or should not affect their treatment in society.

Values and goals: Participants’ values, life goals, and goals for the next month are assessed during assessments at 12 and 24 months.

### Intervention

All young men in a neighborhood are assigned to the same condition. Participants will be removed from the study if they directly threaten or are physically violent toward any study staff or other participants, or if they are seriously disruptive or verbally abusive to peers or staff during soccer training, a soccer game, or assessment at least three times in a 2-week period. On a weekly basis, participants in the intervention conditions are tested for substance use. Any participant with a positive drug or alcohol screen is barred from attending the intervention that day.

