#### Fifteen outcomes

We have 15 primary outcomes: 1) Alcohol Use Disorders Identification Test (AUDIT-C) score < 3 (i.e., problematic alcohol use); 2) no alcohol usage in last 24 h; 3) PEth Alcohol Test (excessive alcohol use in prior 3 weeks, at 24 months only); 4) no marijuana (dagga) usage in the last 10 days assessed via RDT; 5) no quaalude (mandrax) usage in the last 2–3 days assessed via RDT; 6) no methamphetamine (tik) usage in the last 1–2 days assessed via RDT; 7) HIV testing in the last 3 months; 8) employment (part/full-time); 9) income above 1200 ZAR/month; 10) no concurrent partnerships; 11) no sex without condoms; 12) no violent acts toward women; 13) no arrests by police; 14) engaged in a community activity; and 15) Center for Epidemiologic Studies of Depression (CES-D) score < 16 (i.e., caseness). Each primary outcome measure is a binary variable (not present or present).

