#### Condition 1: control condition (CC)

Following the baseline interviews, young men in the eight neighborhoods randomized to the control condition (*n* = 400 men) routinely receive flyers with picture stories regarding HIV prevention strategies and how to access these strategies locally: HIV testing, circumcision, HIV treatment including ARV, condoms, and STI testing and treatment. These young men are only contacted for assessments 6, 12, and 24 months later following the baseline interview.

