#### Condition 2: soccer league (SL)

All young men in eight neighborhoods (*n* = 400) receive soccer training for 1 year. After all of the baseline assessments are completed in a specific neighborhood, soccer coaches visit each participant individually to describe the intervention in detail, invite them to the soccer league, and answer any questions. The league includes at least two and usually three teams per neighborhood (14 men minimum per team needed, anticipating some absenteeism), resulting in approximately up to 24 teams in this condition. Each week, there are 2 days of practice and 1 day for a game with another team. Teams are led by coaches who are recruited from the broader township (versus target neighborhoods) to safeguard players’ confidentiality (coming from the same neighborhood is likely to inhibit men’s disclosures about problem issues, fearing the coach may tell others). Coaches cannot be regulars at the local shebeens or known drug addicts, and must have held a job at some time previously, have experience playing soccer, and demonstrate good social skills. In this way, coaches are positive peer deviants (i.e., role models) for participants [53, 54]. About 30% of persons applying to be coaches are hired, based on initial interviews and observations completed during the coach training.

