#### Condition 3: soccer league and vocational training (SL-V)

For the first 6 months of intervention delivery, all procedures described above for the SL condition are replicated for all young men in eight neighborhoods (*n* = 400 men). The selection, training, and monitoring system for coaches and participants is the same in both conditions for the first 6 months, with soccer offered 2 days per week and a game on Saturdays.

After 6 months, all young men are offered vocational training through either Silulo Ulutho Technologies or Zenzele Training and Development programs. In these programs, participants have access to accredited training programs in public computer courses, woodwork, and welding. Both programs are located in Khayelitsha, which is close to participants’ homes, thus avoiding transport-related barriers. Additionally, the training programs occur in a mentor-mentee context so that participants can develop the interpersonal skills required for employment.

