### Missing data

We will analyze: 1) missing data longitudinally as a binary outcome at 6, 12, and 24 months, omitting the first time point; 2) separately, we will analyze which men drop out as a single binary outcome. Baseline sociodemographic variables (e.g., age, education) will be examined as predictors in each analysis; and 3) we will use intervention conditions as predictors of baseline sociodemographics. Any significant variables (analyses 1 and 2) and any sociodemographics that are predicted by condition (analysis 3) will be collected together and used as additional predictors in sensitivity analyses when assessing significance of the conditions.

Additional information is available as counts for several outcomes (e.g., number of days of drug use, number of partners) and continuous variables (CES-D, AUDIT) which we will analyze in secondary analyses. Among the subset of HIV-positive participants, we will analyze the HIV treatment continuum variables (i.e., linkage and retention in care, uptake and adherence to ARV). For binary outcomes measured at baseline and 6, 12, and 24 months, we expect to treat time categorically, and model main effects for condition, time, and time by condition interaction. Primary interest is the differences among conditions in the change from baseline to 12 months and to 24 months, and secondarily the change to 6 months. Assuming significant differences between conditions in changes from baseline, we will estimate pairwise differences (SL-V minus SL; SL minus CC; SL-V minus CC) in changes from baseline to months 6, 12, and 24.

Finally, we will summarize the frequency of practice elements delivered by coaches from process monitoring data in tables overall and by coach. We wish to see if supervisor ratings are predictive of practice element data that we collect; the model is longitudinal repeated measures but with coaches as the subject. Also, using GLMMs, we will analyze the process measures that are measured regularly (daily/weekly/monthly) during the soccer intervention to compare SL and SL-V conditions and to see how they relate to future employment. We expect that coaches who most frequently use goal setting and problem solving will have the young men with the greatest improvements. One year after the completion of data collection, a data set stripped of potential identifiers will be provided to the National Institutes of Health and available at UCLA.

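### Removal for violence or disruption is from the study, not only from sessions, so follow-up can be lost almost only in the two soccer arms; the size is unknown, but the wording should be changed

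*Protocol article*

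**What the plan says.** The rule stands in the Intervention section of the protocol article: "Participants will be removed from the study if they directly threaten or are physically violent toward any study staff or other participants". A second limb covers men who are seriously disruptive or verbally abusive "during soccer training, a soccer game, or assessment at least three times in a 2-week period". A few lines later the same section sets a narrower consequence for a positive drug or alcohol screen: the man misses that day's intervention only. The article therefore distinguishes exclusion from a session from removal from the study, and uses the latter here. It does not say that removed men are still assessed.

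Exposure to the rule differs by condition:
- Control: "These young men are only contacted for assessments 6, 12, and 24 months later following the baseline interview".
- SL: men "receive soccer training for 1 year", and "Each week, there are 2 days of practice and 1 day for a game with another team".
- SL-V: "For the first 6 months of intervention delivery, all procedures described above for the SL condition are replicated"; vocational training is offered after that.

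The 15 outcomes include "12) no violent acts toward women; 13) no arrests by police", together with three urine drug tests. For attrition, the Missing data section says "Baseline sociodemographic variables (e.g., age, education) will be examined as predictors in each analysis". Variables found significant there, or unbalanced by condition, enter sensitivity analyses as covariates.

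**The concern.** A conduct rule that stops outcome collection is harmless to the comparison if it operates equally in all arms, or if it is unrelated to outcome. Neither can be assumed here. Men who meet staff and peers three times a week have far more occasions to trigger the rule than men seen three times in two years. The behaviour that triggers it (threats, violence, abuse) plausibly goes with worse results on some of the 15 outcomes. If so, the active arms would lose some of their worst-scoring men and control would not, which would favour the active arms.

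Two further things are at stake. The primary result needs only three of 15 outcomes to be significant, and one set of removals can shift several of them together. The Data monitoring section would stop the trial only for apparent iatrogenic effects of men meeting in groups, so the men in whom such harm might show are the ones whose later data would be missing.

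**Working it through.** **1. Opportunity to trigger the rule** (scheduled contacts after baseline, assuming full attendance)

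- SL: 3 × 52 = 156 sessions, plus 3 assessments = 159.
- SL-V: at least 3 × 26 = 78 sessions, plus 3 assessments = 81; vocational training is extra.
- Control: 3 assessments.
- Ratios to control: 159/3 = 53 and 81/3 = 27.

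Any two weeks of soccer contain 6 sessions. In control at most one scheduled visit falls in any two weeks, so the three-incident limb can hardly be met there unless several incidents within one visit are counted. The violence limb needs only one event and can apply at a control assessment, but with far fewer occasions and no group sessions with other participants.

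**2. Effective sample size, from the plan's own figures**

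For 30% versus 17%, two-sided alpha 0.05, 80% power and continuity correction, n = 181 per arm. Inflated: 181 × 1.7284 / 0.80 = 391 per arm, close to the stated 400. With 20% loss, the effective n is 400 × 0.80 / 1.7284 = 185 per arm.

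**3. Crude bias with no true effect**

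Let p be the true failure rate in both arms, r the share of an active arm removed, and q the share of removed men who would fail. The observed failure rate in the active arm is (p − rq)/(1 − r). All three inputs are assumptions; the article gives no removal rate.

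With p = 0.30 and q = 1:
- r = 2%: (0.30 − 0.02)/0.98 = 28.6%, a spurious benefit of 1.4 points.
- r = 5%: (0.30 − 0.05)/0.95 = 26.3%, a spurious benefit of 3.7 points.

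Rejection rate for one outcome and one pair of arms, worked for r = 5%, q = 1: mean rate (0.300 + 0.263)/2 = 0.282; SE = √(2 × 0.282 × 0.718 / 185) = 0.0468; z = 0.0368/0.0468 = 0.79; rejection = 1 − Φ(1.96 − 0.79) + Φ(−1.96 − 0.79) = about 12%.

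| Removed (p = 0.30) | Benefit, q = 1 | Rejection | Benefit, q = 0.7 | Rejection |
|---|---|---|---|---|
| 1% | 0.7 points | 5.3% | 0.4 points | 5.1% |
| 2% | 1.4 points | about 6% | 0.8 points | 5.3% |
| 5% | 3.7 points | 12.4% | 2.1 points | 7.3% |
| 10% | 7.8 points | 39.9% | 4.4 points | 15.9% |

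At 5% removal and q = 1, the benefit is 4.2 points for p = 0.20 and 3.2 points for p = 0.40.

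**4. Allowing for baseline**

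The planned model uses baseline data. Assume a baseline to 24-month correlation of 0.5 and p = 0.30 at both times. The probability of failing at both times is 0.09 + 0.5 × 0.21 = 0.195, and of failing at 24 months only is 0.105. Remove 5% of the arm, all 24-month failures: 0.0325 had failed at baseline and 0.0175 had not. The observed rates are 0.1625/0.2675 = 0.607 and 0.0875/0.6825 = 0.128. Standardised to baseline: 0.3 × 0.607 + 0.7 × 0.128 = 27.2%, a bias of 2.8 points instead of 3.7. At 2% removal the same steps give 1.1 instead of 1.4. If removal depended on baseline status alone, the bias would be zero.

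**5. Effect on the three-of-15 rule**

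Simulation with 15 test statistics correlated at 0.1, five of them shifted as in step 3, one pair of arms and effective n 185. The chance of three or more significant outcomes is about 4% with no removal, 5% at 2% removal with q = 1, 6% at 5% with q = 0.7, and 10% at 5% with q = 1.

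**The case against.** The case against a stronger reading is good, and most of it stands.

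- A reader might infer that men who use drugs, or are arrested, disappear from the soccer arms. The text does not support this. A positive screen bars a man for that day only, and arrest is not a trigger. The violence outcome concerns women, while the rule concerns staff and other participants. The link to outcomes is a plausible correlation, in line with the Background's view that these men's risks cluster, and no more.
- A reader might infer that control men cannot be removed. They can: the rule names assessments, and a single violent act suffices.
- A reader might infer that both soccer arms have 156 sessions. That holds for SL only; for SL-V the article supports at least 78.
- A reader might infer that harm is hidden from the monitoring board. Triggering incidents happen in front of staff, coaches report daily, and serious adverse events, including criminal acts, go to investigators, ethics boards and funders within 48 hours. What would be thinned is later outcome data.
- The magnitude rests on assumed inputs, with q = 1 as the extreme. At 1–2% removal the bias is small, and the mixed model can recover part of it from baseline and pre-removal data.
- The article is condensed, and the full protocol may say how removed men are followed up.

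The last point does not dispose of the matter. The article states a rule about who stays in the study, and the contrast with the same-day bar makes it hard to read as meaning sessions only. Nor can the planned attrition analyses be relied on: they use baseline sociodemographics, whereas removal follows from behaviour during the intervention, which is not comparably observed in control.

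**Conclusion.** The concern holds in a limited form. As worded, the rule produces loss of follow-up that depends on arm, through 27 to 53 times more scheduled contacts in the soccer arms. It plausibly also depends on outcome. That second step is inference, and the first assumes that removal from the study ends assessment.

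The size cannot be known from the article. With a 30% failure rate and every removed man a failure, the crude spurious benefit is 1.4 points at 2% removal and 3.7 at 5%, set against the 13-point difference (30% to 17%) used in planning. It falls to about 1.1 and 2.8 points if baseline is conditioned on with a correlation of 0.5, and to 0.8 and 2.1 crude points if 70% of removed men would fail. The bias is negligible to small at 1–2% removal and begins to matter from about 5%.

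This should be fixed but is not a must-fix. The reason to act is that outcomes never collected cannot be reconstructed, while the change is simple and recruitment was still under way when the article was submitted.

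**What to change.** State in the Intervention section that meeting these criteria ends participation in intervention sessions but not follow-up. The criteria themselves can stay as they are; whether and when a man is kept from sessions is a safety matter not judged here. Then:

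- continue the 6-, 12- and 24-month assessments where this is safe, by telephone if needed;
- analyse these men in their randomised condition;
- report the number and timing of removals by arm, including to the monitoring board;
- add a sensitivity analysis counting removed men with missing outcomes as failures. Because removals will fall mostly in the soccer arms, this acts as a pessimistic bound for them.

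If the full protocol already provides for follow-up of removed men, aligning the article's wording with it is enough.

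Cost: an amendment approved by both ethics boards, a registration update, and safety arrangements for what may be a few assessments. Telephone assessments would lose the breath, PEth and urine results, which are outcomes 2 to 6, or five of the 15. For those outcomes the sensitivity analysis remains necessary.

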#### Condition 1: control condition (CC)

Following the baseline interviews, young men in the eight neighborhoods randomized to the control condition (*n* = 400 men) routinely receive flyers with picture stories regarding HIV prevention strategies and how to access these strategies locally: HIV testing, circumcision, HIV treatment including ARV, condoms, and STI testing and treatment. These young men are only contacted for assessments 6, 12, and 24 months later following the baseline interview.

#### Condition 2: soccer league (SL)

All young men in eight neighborhoods (*n* = 400) receive soccer training for 1 year. After all of the baseline assessments are completed in a specific neighborhood, soccer coaches visit each participant individually to describe the intervention in detail, invite them to the soccer league, and answer any questions. The league includes at least two and usually three teams per neighborhood (14 men minimum per team needed, anticipating some absenteeism), resulting in approximately up to 24 teams in this condition. Each week, there are 2 days of practice and 1 day for a game with another team. Teams are led by coaches who are recruited from the broader township (versus target neighborhoods) to safeguard players’ confidentiality (coming from the same neighborhood is likely to inhibit men’s disclosures about problem issues, fearing the coach may tell others). Coaches cannot be regulars at the local shebeens or known drug addicts, and must have held a job at some time previously, have experience playing soccer, and demonstrate good social skills. In this way, coaches are positive peer deviants (i.e., role models) for participants [53, 54]. About 30% of persons applying to be coaches are hired, based on initial interviews and observations completed during the coach training.

Figure 4 summarizes the training model for intervention delivery. We do not ask coaches to replicate a manual with fidelity. We train all coaches in the foundational skills and theory common across evidence-based psychotherapeutic interventions [55, 56] and adolescent HIV prevention programs [57], the bottom tier on Fig. 4. Coaches are then trained in specific content areas (i.e., the key messages to be given in the intervention), the middle tier in Fig. 4. This includes training in life skills designed around six topics (reducing alcohol/drug use, increasing HIV testing, routinely getting health check-ups and optimizing interactions with healthcare providers, creating enjoyable and healthy daily routines, building friendship networks that are not based on shared risk behaviors, and managing money (real cost of alcohol/drugs)). Each of these topics is repeatedly rehearsed with role-play during training so that coaches practice delivering health messages. Coaches also practice brief alcohol interventions, and how to acquire information about HIV, tuberculosis (TB), alcohol use, and employment. To better facilitate referrals, coaches visit local clinics to meet their staff and learn about the services provided. Each coach also receives training in an EBI, the Street Smart program, which is a 10-session, small-group intervention for high-risk youth [58–60]. This EBI has been adapted for Uganda and South Africa [61]. Coaches do not replicate the delivery of this intervention with young men, but the training provides a demonstration model for an EBI. HIV EBI share common processes, components, and principles [57, 62]. These procedures are repeatedly reviewed over the entire training program, so that the coaches are very familiar with HIV and substance use prevention and cognitive-behavioral shaping. However, coaches are allowed flexibility in implementing specific activities. Coaches report when, which, and how the practices are used to initiate topics regarding HIV and substance use via mobile phones daily.

